***c) Data Collection and Management***

1. *Data collection procedures*

Study-specific visits will be conducted at the study site by the study nurse, and be timed to coincide with routine health care visits whenever possible. Medical record abstraction will be performed by the study site nurse. Study nurses will be present in each study facility and will be responsible for the collection, maintenance of study records and data, and collection of viral load specimens. Informed consent documents, study screening/enrollment logs, and participant locator forms that include identifiable information will be completed at enrollment and stored in a locked secure location in the health facility with access limited to study staff. After all data collection is completed, the study records will be stored in central storage in EGPAF-Swaziland offices under the same strict controls.

Data will be collected and entered into electronic tablets by direct data entry into a database that will be designed specifically for this study and stored on a secure web-based server. Built-in data checks will ensure that data are within a feasible range. Any out of range values will be verified by looking through the source document. In facilities that do not have wi-fi access for immediate uploading of data, data will be stored temporarily on the tablet, and subsequently transferred to the web-based server on a routine basis. There will be controlled access to the web-based database by study staff with specific IDs and permissions depending on their study role, both for the study team in EGPAF/Swaziland and EGPAF/United States.

1. *Data collection instruments*

The study data collection instruments will be designed in English and pilot tested by the study team prior to use. Some data components in the participant interview may require translation into SiSwati to ensure accurate and consistent interpretation. The management and conduct of study visits will be the responsibility of the site study nurse. The study nurse will work closely with the study coordinator, who will be responsible for oversight of the data collection by study nurses, to ensure quality of the data collected.

Caregiver-child pair information will be collected through caregiver interviews and review of facility, laboratory and patient records. Study nurses will be trained to interview caregivers and abstract data from the facility records using electronic data capture forms. Participant-specific data collection forms will be identified with the participant’s unique study identification number. Participant names will not be included in the study database. All electronic tablets will be password protected, with access to only key study personnel.

*3. Statistical Analysis Plan*

First, we will summarize baseline characteristics of participants using means (standard deviations) or medians (IQR) for continuous variables and proportions for categorical variables, stratified by FAM-CARE/control arms. We will identify characteristics that differ significantly between the two study arms. Since participation in the FAM-CARE program is voluntary, we will assess for potential selection bias in the FAM-CARE sites by comparing characteristics of families that decline to families that accept FAM-CARE.

The primary objective of this study is to evaluate the effect of a FAM-CARE program of HIV care on the proportion of HIV-positive children on ART with viral suppression (defined as viral load below the level of assay detection) and the proportion of HIV-positive children on ART with HIV RNA >1000 copies/mL 18 months after enrollment. We will estimate the respective proportions and associated confidence intervals by study arm. Below we outline potential approaches to estimating the effect of FAM-CARE depending on comparability of the study arms:

a) If the FAM-CARE program decline rate is low (say, <10%) and baseline characteristics of children in FAM-CARE and control sites are fairly similar, we will estimate the proportion of HIV-positive children on ART with viral suppression and associated confidence intervals by study arm. Using a simple chi-square test, we will compare the two proportions at 5% significance level. The proposed chi-square test assumes outcomes from enrolled children are independent.

However, there is potential correlation of viral outcomes of children from the same family as well as children from the same facility, thereby violating the assumption of independence required for validity of the chi-square test. We propose to use multilevel generalized linear models to account for the potential intra-cluster correlation due to family unit and facility. In addition, we will adjust for potential confounding that may arise due to imbalances in children’s characteristics between study arms.

b) If the FAM-CARE program decline rate is substantial (>10%) and baseline characteristics of children differ significantly between those who accept FAM-CARE and those who decline, we propose to use the propensity score method to match and compare FAM-CARE and non- FAM-CARE participants. Using data from the FAM-CARE sites, we will estimate the probability of accepting FAM-CARE program given the baseline children and family characteristics. Using special matching algorithms, we will develop a statistical control group that will be compared with the FAM-CARE group. Regression modeling will be used to estimate the effect of the FAM-CARE group compared to the control group.

c) Finally, we will perform an intent-to-treat analysis in which all children at facilities offering the FAM-CARE program will be compared to all children at facilities without FAM-CARE program.

To answer primary aim 2, we will use the same statistical approach described for specific aim 1 above.

To answer secondary objectives 1 and 3, the analysis for the primary objective described above will be repeated using the appropriate outcomes.

To identify factors associated with viral suppression and HIV RNA >1,000 copies/mL (secondary objective 2), we propose to use multilevel logistic regression models to estimate the association between viral suppression and putative factors in each study arm. Examples of factors that might be evaluated include age and gender of child, when ART initiated and ART regimen, serious illness or hospitalization, timeliness of pharmacy drug pick-up, school attendance, family size, number of other HIV-positive individuals in family, HIV treatment and clinical status of other HIV-positive family members, disclosure of HIV status within family.

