**a. Overview of Study Design**

As part of implementation of the pilot FAM-CARE program in Swaziland, health care facility clusters have been randomized to initiate the pilot FAM-CARE program (two health care facility clusters) or continue to provide the current standard of HIV care with separate pediatric and adult HIV clinics (two health care facility clusters). Our study will be an evaluation of this pilot program. Our program evaluation will enroll and follow a prospective cohort of HIV-positive children from selected FAM-CARE sites and control sites to assess the effects of the FAM-CARE program on retention and viral suppression in HIV-positive children on ART. Clinical care for the children is provided through the program and not the study; the study is to evaluate the effect of the program on pediatric viral suppression and retention in care. The FAM-CARE program (described below) is being implemented under the USAID-funded AIDSFree project; no aspects of this care program will be supported through SOAR funding. The SOAR funding is solely being used to support the research evaluation of the program’s effect on pediatric viral suppression and retention.

1. **Study Relationships/Related Project**

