**c) Overview Table of Data Gathering Activities**

| **Data Gathering Activities** | Prospective Evaluation of FAM-CARE Program | Qualitative Evaluation |  |
| --- | --- | --- | --- |
|  | Randomized study of sites providing FAM-CARE HIV care compared to control standard HIV care | Semi-structured in-depth interviews |  |
| **Study population** | HIV-positive children and their caregiver  Other HIV-positive adults in the family (not required for enrollment of children) | Caregiver, health care workers |  |
| **Sample size** | 666 HIV-positive children (333 per arm) to achieve the target sample size of 444 HIV-positive children receiving ART from unique families (222 per arm) | Individual interviews with a subset of caregivers (15-25) and health care providers (15-25) in the intervention sites |  |
| **Location of activity** | 8 health care facilities (4 control, 4 intervention) in Hhohho region, Swaziland | 4 health care facilities (intervention sites) in Hhohho region, Swaziland |  |
| **Timing** | Project Month 3 (after IRB submission) | Project Month 18 |  |
| **Method** | Data abstraction from medical records; participant interview; specimen collection | Semi-structured interview led by trained research assistant |  |
| **Informed Consent document** | - Consent form for caregiver-child participation in study cohort - Assent form for children - Consent form for medical record abstraction from HIV-positive adults in the family | - Consent form for interview participation for caregivers - Consent form for interview participation for health care providers. |  |
| **Study Instrument** | Data collection tools include:   - At enrollment:   - Contact form   - Enrollment Forms (caregiver and child)   - Family Clinical Data Abstraction Form   - Child Clinical Data Abstraction Form - At each scheduled follow-up visit:   - Follow-up forms (caregiver and child)   - Family Clinical Data Abstraction Form   - Child Clinical Data Abstraction Form - As needed:   - Missed visit form   - Maternal pregnancy-transfer to MNCH care form   - Child mortality form   - Family member mortality form   - Termination form   - Study viral load specimen tracking form   - Study viral load result form | - Qualitative interview guides for caregivers - Qualitative interview guides for health care providers |  |

1. **Data Gathering Activity 1: Prospective Cohort Enrollment to Evaluate the FAM-CARE Program**
2. **Subject Population**

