**Figure 1: Schema of Study Design for the Evaluation of FAM-CARE Program Design:**

**Four clusters of Health Care Facilities/Clinics in Hhohho Region Swaziland**

**Two hospital-based clusters with their filter clinics & two health center-based clusters with their filter clinics**

**Random selection of clusters** **(stratified by whether health center vs hospital cluster) to implement** **family-centered model of care or continue standard care**

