The primary study endpoints are the proportion of children on ART with viral suppression (defined as HIV RNA below the level of assay detection) and the proportion with HIV RNA >1,000 copies/mL at 18 months. The tables below show the minimum number of children receiving ART needed to demonstrate significant (0.05) effects of the FAM-CARE program on viral suppression and HIV RNA >1,000 copies/mL compared to control facility care, assuming different viral suppression and HIV RNA >1,000 copies/mL rates in the control group.

**Table 3** (viral suppression) shows the minimum sample size per arm and overall needed to demonstrate a significant FAM-CARE program effect with 80% power at 5% significance levels, assuming different levels of viral suppression in children on ART from control facilities (ranging between 65-85% suppression) and different levels of improvement that could be observed in children in FAM-CARE program sites compared to control sites. With 398 HIV-positive children receiving ART from unique families, we will have 80% power to detect at least a 10% increase in viral suppression with FAM-CARE, assuming a viral suppression rate between 65% and 80% in control children on ART.

**Table 3.** Sample size estimates for detecting FAM-CARE effects on viral suppression rates

| % Viral Suppression in Control | Minimum Effect of FAM-CARE | % Viral Suppression in FAM-CARE Sites | Alpha | Power | Sample size/ arm | Total sample size | Adjusted for 10% LTFU |
| --- | --- | --- | --- | --- | --- | --- | --- |
| .65 | .15 | .80 | .05 | 80% | 138 | 276 | 308 |
| .65 | .20 | .85 | .05 | 80% | 73 | 146 | 164 |
| .65 | .25 | .90 | .05 | 80% | 43 | 86 | 96 |
| .70 | .15 | .85 | .05 | 80% | 121 | 242 | 270 |
| .70 | .20 | .90 | .05 | 80% | 62 | 124 | 138 |
| .75 | .15 | .90 | .05 | 80% | 100 | 200 | 224 |
| .80 | .10 | .90 | .05 | 80% | 199 | 398 | 444 |
| .85 | .05 | .90 | .05 | 80% | 686 | 1372 | 1526 |

**Table 4** (HIV RNA >1,000 copies/mL) shows the minimum number of children required to detect at least a 5%, 10%, or 15% improvement with FAM-CARE care sites compared to control sites, with 80% power at 0.05 significance level, assuming different HIV RNA >1,000 copies/mL rates in control children (ranging from 10-30%).

**Table 4:** Sample size estimates for detecting FAM-CARE effects on HIV RNA >1,000 c/mL

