| % HIV RNA >1,000 c/mL in Control | Minimum Effect of FAM-CARE | % HIV RNA >1,000 c/mL in FAM-CARE Sites | Alpha | Power | Sample size/ arm | Total sample size | Adjusted for 10% LTFP |
| --- | --- | --- | --- | --- | --- | --- | --- |
| .10 | -.05 | .05 | .05 | 80% | 435 | 870 | 968 |
| .15 | -.05 | .10 | .05 | 80% | 686 | 1372 | 1526 |
| .15 | -.10 | .05 | .05 | 80% | 141 | 282 | 314 |
| .20 | -.05 | .15 | .05 | 80% | 906 | 1812 | 2014 |
| .20 | -.10 | .10 | .05 | 80% | 199 | 398 | 444 |
| .20 | -.15 | .05 | .05 | 80% | 76 | 152 | 170 |
| .25 | -.10 | .15 | .05 | 80% | 250 | 500 | 556 |
| .25 | -.15 | .10 | .05 | 80% | 100 | 200 | 244 |
| .30 | -.10 | .20 | .05 | 80% | 294 | 588 | 654 |
| .30 | -.15 | .15 | .05 | 80% | 121 | 242 | 270 |

We have adjusted the effective sample size to account for a possible 10% loss to follow up over the 18-month study period. Our estimation assumes enrolment of one HIV-positive child on ART per household and that there is no correlation of children’s viral load outcomes within facilities.

Assuming 10% loss to follow-up, we plan to enroll 444 HIV-positive children receiving ART from unique family units into the study over 12 months. With this sample size, we have power to detect a minimum of 10% increase from an estimated proportion of viral suppression of 80% in the control sites to 90% in the FAM-CARE sites or 15% increase in viral suppression with FAM-CARE if control rate of suppression is 75% or lower (Table 3 highlighted rows) and a minimum reduction in HIV RNA >1,000 copies/mL rates from 20% in the control sites to 10% in the FAM-CARE sites or from 15% in the control sites to 5% in the FAM-CARE sites (Table 4 highlighted rows).

*Study sampling procedures*

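### The planned primary analyses stop at facility and family and never use the four randomised clusters, so p-values and intervals are too optimistic whenever outcomes vary between clusters

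*Protocol*

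**What the plan says.** **Randomised unit.** The Overview of Study Design states: "health care facility clusters have been randomized to initiate the pilot FAM-CARE program (two health care facility clusters". The other two clusters continue standard care. Figure 1 adds that selection was "stratified by whether health center vs hospital cluster", so each arm holds one hospital cluster and one health-centre cluster. Within each cluster only the parent facility and its largest filter clinic enrol, which gives "8 health care facilities (4 control, 4 intervention) in Hhohho region, Swaziland".

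**Primary analysis.** Section 3, Statistical Analysis Plan, offers approaches whose choice depends on the programme decline rate and on baseline comparability.
- Route (a): "Using a simple chi-square test, we will compare the two proportions at 5% significance level". The following paragraph says that correlation within family and within facility breaks the independence this test needs, and continues: "We propose to use multilevel generalized linear models to account for the potential intra-cluster correlation due to family unit and facility". It then promises adjustment for confounding that arises from imbalances between arms.
- Route (b) is propensity-score matching on acceptance of the programme.
- Route (c) is an intent-to-treat comparison of facilities with and without the programme, with no method given.

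None of the three mentions the randomised cluster, the hospital/health-centre stratum, or a reference distribution suited to few clusters.

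**Enrolment viral load.** Study Procedures and Table 5 have it drawn from every child on ART at enrolment and at 6, 12 and 18 months. The primary analysis does not name it as a covariate. The baseline paragraph of the same section says: "We will identify characteristics that differ significantly between the two study arms".

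**The concern.** Chance favours or harms a whole cluster at once: the parent facility and its filter clinic share assignment, referral links and region-level support. A model whose highest level is the facility treats the two as independent evidence about the programme. It sees eight units where the randomisation produced four. The chi-square goes further and sees each child as a unit.

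With two clusters against two, ordinary differences between sites can pass for a programme effect. The protocol intends to work with the Ministry of Health on wider roll-out if the programme is found effective, so the false-positive rate matters. The baseline value of the primary outcome, which would do most to separate existing site differences from a programme effect, has no prespecified place in the analysis.

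**Working it through.** **1. Inputs.** From the protocol: four clusters, two per arm; eight facilities; suppression of 80% versus 90%; 5% significance and 80% power (sidedness is not stated, but the table reproduces as two-sided); 10% loss to follow-up; zero correlation within facilities. Not in the protocol, so assumed: a cluster-level ICC, taken over 0.005 to 0.05.

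**2. The stated sample size reproduces, but only for independent children.** With pooled variance and no continuity correction:

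n per arm = [1.96·√(2·0.85·0.15) + 0.842·√(0.8·0.2 + 0.9·0.1)]² / 0.10² = 199.

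The total is 398. For dropout, 199/0.9 rounds up to 222 per arm, or 444. This matches Table 3.

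**3. Chi-square under no effect.** Each randomised cluster supplies m = 199/2 = 99.5 analysed children. The design effect is 1 + (m − 1)·ICC, and the true type I error is 2·[1 − Φ(1.96/√DE)].

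| Cluster ICC (assumed) | Design effect | True SE / naive SE | Type I error |
|---|---|---|---|
| 0.005 | 1.49 | 1.22 | 10.9% |
| 0.01 | 1.99 | 1.41 | 16.4% |
| 0.02 | 2.97 | 1.72 | 25.5% |
| 0.05 | 5.93 | 2.43 | 42.1% |

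Simulation with unequal facilities gives about 17%, 26% and 42-44% at the last three ICCs. Cluster variation alone gives the arm contrast a standard deviation of √(ICC·0.16), which is 4.0, 5.7 and 8.9 percentage points. The target effect is 10 points.

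**4. Facility-level model under no effect.** This was approximated in three ways, all without the family level: unweighted facility means, a moment-based random-effects analysis of facility proportions (sizes proportional to Table 2), and a maximum-likelihood logistic model with a facility random intercept. With all between-site variance at cluster level, the ranges across approximations are:

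| Cluster ICC (assumed) | z reference | t, 6 df |
|---|---|---|
| 0.01 | 12-17% | 5-9% |
| 0.02 | 16-20% | 9-13% |
| 0.05 | 24-34% | 16-25% |

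Where the variance sits changes these figures.
- Split equally between cluster and facility (total ICC 0.01, 0.02, 0.05), the t on 6 df rejects about 7%, 8% and 10% (unweighted means).
- With all of it at facility level, the t on 6 df shows no inflation (about 5% or below). The chi-square still rejects 13% at a facility ICC of 0.01.
- With no correlation at all, the random-effects and logistic versions reject about 4% with z, but z on eight unweighted means already rejects about 9%. Part of the top of the z ranges therefore comes from the z reference and not from the missing cluster level.

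**5. Cluster-level analysis.** A t-test on the four cluster proportions (2 df, critical value 4.30) rejects about 5% at every ICC tried, and so does the version paired within strata (1 df, critical value 12.71). The price is power. For 80% versus 90%, the non-central t has noncentrality 0.10/√(0.25·DE/199), which is 0.10/0.0354 = 2.82 at ICC 0:

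| ICC | 2 df | 1 df |
|---|---|---|
| 0 | 36% | 18% |
| 0.01 | 22% | 13% |
| 0.02 | 17% | 11% |
| 0.05 | 11% | 8% |

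The stratified randomisation has 2 × 2 = 4 possible allocations, so the smallest two-sided randomisation p-value is 2/4 = 0.5.

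**The case against.** The strongest reply has four parts.

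*The protocol already steps back from the chi-square.* It says the independence assumption is violated and proposes a multilevel model, so that model is the natural operative analysis. This is fair: the 17/26/42% figures describe the chi-square and should not be read as the error rate of the multilevel model. What stands is that the chi-square is never withdrawn and no text says which result decides.

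*The size of the facility-model inflation depends on assumptions.* This also stands. The documents give no ICC and do not say how between-site variance divides. A reader might infer that the facility model must be badly anti-conservative; the working does not support that if variance lies between facilities and not between clusters. The direction holds whenever some of it lies between clusters.

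*Route (a) may not be the one used.* The protocol expects 10-20% non-participation and assumes 20% refusal when sizing enrolment, so the propensity route could well be triggered, and the intent-to-treat comparison is run in any case. Neither brings in the randomised cluster, so the gap remains.

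*Viral load.* A reader might infer that enrolment viral load enters only if a baseline significance test is positive. The documents do not say so. The sentence on significant differences belongs to the baseline description, while the adjustment sentence refers to imbalances and names no test or threshold. A separate SAP may also list covariates. The supportable statement is narrower: the variable is not named, and as written it would enter only through imbalance-driven adjustment.

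**Conclusion.** The point holds. The protocol names its test, its significance level and its model levels, and those levels stop below the unit that was randomised. This is a stated choice, not a detail left to a later document. The direction of the error is firm if outcomes vary at all between clusters.

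Its size rests on an assumed ICC and on where the variance lies. With all of it at cluster level and ICC 0.01 to 0.05, type I error is roughly 17% to 42% for the chi-square, 12% to 34% for a facility-level z analysis and 5% to 25% for a facility-level t on 6 df. The facility-level excess falls to about 7-10% with t under an equal split, and disappears with t if all the variance is between facilities.

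A reader might infer that adding a cluster level cures the problem. It corrects the inference but cannot recover the planned power. Two clusters per arm is a limit of the design, and the 80% power statement applies only to independent children.

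**What to change.** 1. Withdraw the chi-square as an inferential test; proportions by arm can stay as description.
2. Base the primary interval and p-value on the randomised cluster, with one degrees-of-freedom rule fixed in advance: 2 df for the unpaired comparison of four clusters, or 1 df if the average of the hospital-pair and health-centre-pair differences is the headline. These are different analyses and only one should be chosen. Under either, report the two within-pair differences descriptively. Apply the same rule to routes (b) and (c).
3. Prespecify adjustment for enrolment viral load (undetectable yes/no) for children on ART at entry. Show the unadjusted estimate beside it, because FAM-CARE was implemented before the study began and the enrolment value may already carry some programme effect.
4. Restate the power. For 80% versus 90% it is at most about 36% (2 df) or 18% (1 df) even at ICC 0. Present the result as estimation with limited confirmatory strength.

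The cost is revised wording and a modest amount of analysis, with no new data. The real price is much wider intervals and giving up the claim of an 80%-powered confirmatory test at this number of clusters.

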**Follow-up: 18 months**

Our primary endpoints of viral suppression and HIV RNA >1,000 copies/mL will be evaluated among HIV-positive children entering the study who are initiating or receiving ART. The sample size will be powered to detect a difference in viral suppression/HIV RNA >1,000 copies/mL in children receiving ART in the FAM-CARE sites to those receiving ART in control sites. For HIV-positive children entering the study who are not currently on ART, we will be able to compare retention in care and the proportion of children initiating ART between those enrolled in the FAM-CARE sites to those in control sites.

At FAM-CARE sites, it is estimated that 10-20% of HIV-positive children may not be enrolled in the FAM-CARE program, because of disclosure or other issues within the family. These children will still be enrolled in the prospective cohort as long as there is >1 family member who is also HIV-positive; we will be able to compare suppression/ART failure/retention rates between children in FAM-CARE sites enrolled in the FAM-CARE program and not enrolled in the FAM-CARE program, although the study will not be powered based on this comparison. We will also be able to compare overall rates of viral suppression/HIV RNA >1,000 copies/mL among all children (regardless of actual participation in FAM-CARE programs) seen at facilities with the FAM-CARE program to those in control facilities.

An individual family may have more than one HIV-positive child, and more than one HIV-positive child that is receiving treatment; based on a review of pediatric enrollment at two sites, it is estimated that ~15% of HIV-positive children come from families with more than one child receiving ART. Viral suppression rates in children from families with more than one child on treatment may be correlated, particularly in the FAM-CARE program. We will create a “family identification number” that will be used at both FAM-CARE and control sites to identify children enrolled in the study who come from the same family, which will allow controlling for potential correlation during analysis.

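### No primary analysis is named for either primary endpoint; at the planned 20% refusal the by-arm branch closes, and a participation-based matched comparison can become the effect estimate

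*Protocol*

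**What the plan says.** All of this is in the Protocol, under Data Collection and Management, item 3 (Statistical Analysis Plan), unless noted.

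- The effect of FAM-CARE on the primary endpoints is to be estimated by one of several possible approaches, "depending on comparability of the study arms".
- Branch (a) applies "If the FAM-CARE program decline rate is low (say, <10%) and baseline characteristics of children in FAM-CARE and control sites are fairly similar". It compares proportions by study arm with a chi-square test. A multilevel model for family and facility correlation is then proposed.
- Branch (b) applies "If the FAM-CARE program decline rate is substantial (>10%) and baseline characteristics of children differ significantly" between children whose families accept the programme and those whose families decline. In that case "we propose to use the propensity score method to match and compare FAM-CARE and non- FAM-CARE participants". On the score itself: "Using data from the FAM-CARE sites, we will estimate the probability of accepting FAM-CARE program". The text does not say where the matched control group is drawn from.
- Item (c) has no trigger: "Finally, we will perform an intent-to-treat analysis in which all children at facilities offering the FAM-CARE program will be compared" with all children at the other facilities.
- The same scheme is carried over to the second primary aim and to secondary objectives 1 and 3.

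On uptake, the Subject Population section says "it is estimated that 10-20% of HIV-positive children may not be enrolled in the FAM-CARE program" at FAM-CARE sites, and Study sampling procedures builds the enrolment target on 20% refusal. The Subject Population section also says that the study is powered on children on ART at FAM-CARE sites against those at control sites, and that the comparison of joiners with non-joiners within FAM-CARE sites is not powered.

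**The concern.** Clusters were randomised and the sample size was set for a comparison between sites. The analysis text nevertheless lets observed uptake and baseline significance tests decide which comparison answers the primary objective, and it ranks none of them. The branch triggers also do not address the same question. The opening sentence and branch (a) concern comparability of the two arms, whereas branch (b) is triggered by differences between acceptors and decliners inside one arm.

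If branch (b) supplies the headline estimate, the contrast is by participation. Joining the programme requires willingness to disclose HIV status within the family, and the protocol lists disclosure among the factors that may be associated with suppression. Families who join may therefore do better whatever the programme does. Matching removes measured differences only. The report could also carry a matched estimate and an intent-to-treat estimate that disagree, with nothing in the plan to say which one counts.

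**Working it through.** **Inputs.** Table 3: 80% against 90%, alpha 0.05, power 80%, 199 per arm, 398 in total, 444 with 10% loss. Subject Population: 10-20% non-participation. Study sampling procedures: 20% refusal, 15% of families with more than one enrolled child, 15% of children not on ART, 666 enrolled. The 10-20% in the programme description is not used, because it includes children with no HIV-positive relative, who cannot enter the study.

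**Reproducing the plan's figures.** n = [1.96·√(2p̄q̄) + 0.8416·√(p1q1+p2q2)]² / (p2−p1)². With p1 = 0.80, p2 = 0.90, p̄ = 0.85: (0.990 + 0.421)² / 0.01 = 199 per arm. Then 199/0.9 gives 222 per arm, 444 in total. The enrolment figure reproduces as 444 × (1 + 0.20 + 0.15 + 0.15) = 666, so 20% refusal is one of its inputs.

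**Is branch (a) open?** Exact binomial probability that observed decline exceeds 10%:

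| True decline | 222 children (23 or more) | 333 children (34 or more) |
|---|---|---|
| 10% | 46% | 48% |
| 12% | 80% | 86% |
| 15% | 98% | 99.6% |
| 20% | about 100% | about 100% |

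At the planned 20%, branch (a) is closed. At the bottom of the expected range it is about an even chance.

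**Does branch (b) then open?** Only if acceptors and decliners also differ significantly. The protocol gives no figure for this. If they did not differ at all, the chance of at least one p<0.05 among k independent covariates is 1 − 0.95^k: 23%, 40% and 54% for k = 5, 10 and 15 (assumed numbers). Real differences would raise it. Where decline exceeds 10% without such differences, or is below 10% with dissimilar arms, only (c) applies.

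**Selection bias with no programme effect.** Assume 80% suppression over the whole site. Acceptor rate = (0.80 − d × decliner rate)/(1 − d), with d the decline rate.

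- d = 0.20, decliners at 60%: (0.80 − 0.12)/0.80 = 85.0%, +5.0 points against control sites at 80%.
- d = 0.20, decliners at 70%: (0.80 − 0.14)/0.80 = 82.5%, +2.5 points.
- d = 0.10, same decliner rates: 82.2% and 81.1%, +2.2 and +1.1 points.

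These are before matching. How much matching would remove cannot be known from the documents.

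**Power of the as-randomised comparison at 199 per arm.** If 90% is the whole-site rate, it is 80% as planned. If 90% is the acceptor rate and decliners stay at 80%, the site rate is 0.80 + 0.10(1 − d), and power = Φ{[√n·(p2−p1) − 1.96·√(2p̄q̄)] / √(p1q1+p2q2)}.

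| Decline | Site rate | Power | Needed per arm | Total with 10% loss |
|---|---|---|---|---|
| 10% | 89% | 70% | 253 | 564 |
| 15% | 88.5% | 64% | 288 | 640 |
| 20% | 88% | 59% | 329 | 732 |

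None of these figures allows for clustering by facility.

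**The case against.** The best defence is that the randomised comparison is not lost. Item (c) is a firm commitment without a trigger, branch (a) is also by study arm, and proportions with confidence intervals are promised by arm before any branch is reached. Being listed last is a position, not a stated rank. All of this stands. The defect is the missing designation of a primary analysis, not a missing analysis.

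Several stronger readings are tempting but not supported:

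- A reader might infer that branch (b) is the expected analysis. The planned refusal rate meets only its first condition; nothing in the protocol quantifies the second.
- A reader might infer that some outcomes of the triggers leave no analysis at all. Item (c) covers them.
- A reader might assume that decliners are the matched controls. With 20-40 evaluable decliners (10-20% of 199), power for 80% against 90% would be 14-24% under 1:1 matching, or 31-43% using all decliners, and the unadjusted bias at 20% decline would be +12.5 to +25 points. But the source is not stated. A score fitted in FAM-CARE sites could be applied to control-site children; with 159-179 acceptors matched 1:1 to them, power is 71-76%.
- A reader might conclude that the 5% error rate is lost. The triggers are uptake and baseline covariates, not outcomes, and no inflation has been shown. What can be supported is selection bias in (b) and two unranked results.

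**Conclusion.** The concern holds as a failure to fix the primary analysis. For both primary endpoints the protocol lists approaches selected on observed decline and baseline comparisons and names none as primary. At its planned 20% refusal, branch (a) is closed. If acceptors and decliners also differ significantly, a matched comparison by participation, with an undefined control pool, can serve as the effect estimate. That is not the site-level contrast on which the sample size rests.

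Under the assumptions shown (no effect, 80% overall, 20% decline, decliners at 60-70%), selection alone gives +2.5 to +5 points against control sites before matching, a quarter to a half of the 10-point target. The decliner rates are assumptions; the decline rates are the protocol's own. The closing of branch (a) is near certain at 15-20% decline and about even at 10%.

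**What to change.** Name one unconditional primary analysis for both primary endpoints: all enrolled children on ART at FAM-CARE facilities against all those at control facilities, whether or not the family joined, using the multilevel model already planned for family and facility correlation. Delete the 10% and baseline-significance triggers. Label the propensity-matched analysis secondary, and state whether its controls are decliners or control-site children. Carry the same order over to secondary objectives 1 and 3. State whether the 90% in Table 3 is a whole-site rate, as the column heading says, or an acceptor rate.

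The cost is wording; no new data are needed. The estimate becomes the effect of offering the programme, so 10 points among joiners would appear as 8-9 points at 10-20% decline if decliners do not change. If 90% is the whole-site rate, power stays at 80%. If it is the acceptor rate, the shortfall in the last table applies and the sample size needs a decision.

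This change should not be used to bring in a rule that counts lost children as not suppressed. It answers nothing raised here and can mislead. With 80% true suppression in both arms, 15% against 5% lost and half of the lost suppressed (all assumed), it gives 0.80 − 0.075 = 72.5% for control and 0.80 − 0.025 = 77.5% for FAM-CARE, a spurious +5.0 points. Complete cases give 0.725/0.85 = 85.3% against 0.775/0.95 = 81.6%, a 3.7-point error the other way.
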